#### Setting

The prospective cohort study will take place in at least eight consultant-led obstetric units in the UK. More than 93% of pregnant women in the UK deliver in consultant-led units.^5 6^ The vast majority of women with symptoms of preterm labour will present to a consultant-led unit for assessment, either directly or following advice from their community midwife or general practitioner.

The study will not include any community maternity units (staffed by midwives, with or without involvement of non-obstetric medical staff), which cover a small proportion of women, mainly in remote and rural areas. In the Perinatal Collaborative Transport Study of perinatal transfers in Scotland,^7^ which involved 52 727 births, only 69 (0.13%) women were transferred to a consultant-led obstetric unit from community maternity units, and only a proportion of these were for suspected preterm labour. The small number of women cared for in community maternity units means their inclusion would not be an efficient use of study resources.

Given that management of women with symptoms of preterm labour and interhospital transfer patterns are likely to vary depending on level of available neonatal care and distance to transfer, we will include a mixture of hospitals with different levels of neonatal care facilities in both rural and urban settings. We will include units with special care units (providing special care for their own local population), local neonatal units (providing special care and high dependency care and a restricted volume of intensive care) and neonatal intensive care units (larger intensive care units providing the whole range of medical, and sometimes surgical neonatal care for their local population and for babies and their families referred from the neonatal network in which they are based, and other networks when necessary). The hospitals will be chosen from different geographical settings (rural/urban) and from different regions of the UK.

If additional units wish to participate in the study, we will consider including them, to increase recruitment rates. The UK Reproductive Health and Childbirth specialty group (clinical study group) have contributed to the study protocol and support the proposed trial.

#### Participant selection and enrolment

Women with signs and symptoms of preterm labour will be identified on presentation to obstetric services. A member of clinical staff, usually the doctor or midwife assessing the woman, will identify potentially eligible participants, provide a participant information leaflet and invite consent. A suitably trained member of clinical staff (doctor or midwife) or research team will consent participants.

Posters and leaflets will be situated in antenatal areas of participating hospitals to alert women that the study is taking place, and women will be allowed as much time as possible to consider participation without unduly delaying further clinical assessment. Participants will receive adequate oral and written information and appropriate participant information and informed consent forms will be provided.

#### Screening for eligibility

The clinical likelihood of preterm delivery is usually evaluated by history and examination, which includes abdominal palpation, to assess strength and frequency of uterine contractions. If preterm labour is suspected, a vaginal speculum examination is performed where the cervix is inspected for dilatation, and evidence of vaginal bleeding and membrane rupture assessed. Swabs for fFN are usually taken at this point. Potential participants in the QUIDS study will be identified after the initial assessment and provided with information about the study. A combined ‘Screening and Consent Form’ will be used as a self-screening tool for potentially eligible participants. Informed consent will take place before speculum examination and the fFN swab has been taken. This approach means that samples are collected at routine speculum examination, as they would be if fFN is implemented in clinical practice, and participants avoid an additional vaginal examination.

#### Ineligible and non-recruited participants

Certain exclusion criteria can only be assessed at speculum examination (eg, vaginal bleeding or evidence of ruptured membranes), so a proportion of women will not be eligible for fFN testing after consent is given. These women will still be enrolled and delivery outcomes collected. The decision whether to use this data for analysis will be the decision of the chief investigator and statisticians.

#### Withdrawal of study participants

Women will be able to withdraw consent for us of their data at any time until the end of the study.

#### Study assessments (see table 1)

**Table 1 T1:** QUIDS study assessments

Visit	Attendance with signs and symptoms preterm labour			
	Screening and recruitment	24–48 hours	1–6 months	Delivery
Inclusion/exclusion criteria	◉			
Participant information sheet	◉			
Consent form	◉			
Demographics	◉			
Obstetric history	◉			
Symptoms and signs	◉			
Quantitative fetal fibronectin (concentration ng/mL)	◉			
Cervical length scan (if available)	◉			
State Trait Anxiety Inventory Questionnaire	◉	◉		
Delivery details				◉
Neonatal outcomes				◉
Qualitative Acceptability Questionnaires (subgroup n=30)			◉	

##### Eligibility assessment (screening and recruitment)

Women presenting with signs and symptoms of preterm labour will be identified on presentation to obstetric services. The doctor or midwife assessing the woman will identify potentially eligible participants and provide an invitation letter and short information leaflet.

After the woman has had the opportunity to consider whether she would like to participate, she will be asked to complete the Screening and Consent Form. The clinician will then decide whether the fFN test can be carried out. If the test can be carried out (according to manufacturer’s guidelines), then the participant will be fully enrolled and that their delivery outcomes will still be collected.

If the woman declines to participate and she is willing to provide a reason for this, the reason given will be entered on to an anonymous log. Baseline demographics will be collected on consenting women, together with height and weight, information on medical history, obstetric history, estimated date of delivery and presenting signs and symptoms.

The original consent form will be stored in the Investigator Site File, a copy is given to the woman, a copy added to the medical notes and a copy sent to the Trial Office.

After providing consent, the participant will be asked to complete a short State Trait Anxiety Inventory (STAI) questionnaire and complete a contact details form. They will also be issued with a letter thanking them for taking part in the trial and giving details of the second questionnaire to be completed.

##### Sample collection

Samples for analysis will be taken with an fFN specimen collection kit, which consists of a sterile polyester tipped swab and a specimen transport tube containing 1 mL extraction buffer (an aqueous solution containing protease inhibitors and protein preservatives including aprotinin, bovine serum albumin and sodium azide). During speculum examination the sterile swab will be lightly rotated across the posterior fornix of the vagina for 10 s to absorb vaginal secretions. Samples should be taken before any other swabs (eg, for microbiology) or cervical manipulation and the speculum lubricated with normal saline as other lubricants may interfere with the antibody-antigen reaction of the test. Following specimen collection the swab should be removed, immersed in extraction buffer, the shaft of the swab snapped off and the transport tube sealed.

Before analysis, samples are gently mixed and as much liquid as possible expressed from the swab by rolling the tip against the inside of the tube.

##### Initial fFN test

The sample taken will be run at a near bedside Hologic Rapid fFN 10Q analyser, specially adapted for the QUIDS study. As fFN (or other similar biochemical tests of preterm labour) are part of standard care, it would be unethical to blind clinicians from the qualitative fFN result. The analyser will thus reveal a qualitative fFN result (positive/negative/invalid based on a 50 ng/mL threshold) for clinicians to base clinical decision-making on, according to local protocols. The quantitative fFN result, however, will be stored as a three-letter code, blinding caregivers from the result. Samples will be run as per manufacturers instructions (described above in the section ‘health technologies being assessed’).

##### Repeat fFN tests

If there is clinical indication for further fFN tests (eg, because of ongoing symptoms of preterm labour after 7 days), the results will also be recorded.

##### Labour/delivery/neonatal assessments

Admission for delivery will not be a formal study visit, but data will be collected using information recorded in the participant’s notes. Delivery data will be collected on the maternal outcomes of delivery, including method of delivery, indication for delivery method, onset of labour, date and gestation of delivery and blood loss.

##### Questionnaires

All participants who are eligible to participate will be asked to complete a STAI questionnaire before the speculum examination. The same questionnaire will be repeated on 24–48 hours postexamination. The second questionnaire will be provided on paper with a prepaid envelope to be returned by post to the Trial Office. If not returned by post, the Trial Office may try to contact the participant (with the contact details provided), to complete the questionnaire over the phone.

#### Safety and quality assessments

The Hologic Rapid fFN 10Q analyser has integrated QC measures, and we will keep records of these as well as any additional staff training that occurs after the study starts. It is recommended that a daily precalibrated reusable QC cassette be inserted and analysed every 24 hours to verify that the analyser performance is within specification. A daily QC should be performed if one has not been done in the preceding 24 hours before a patient test is to be done. Logs of results are stored on the machine and can be downloaded, and we will also ask the participating sites to keep a monthly paper log of QC tests done. Each patient test has an internal QC, with a procedural control line that verifies the threshold level of signal by the instrument. Sample flow detection ensures the sample travels across the cassette properly, and confirms absence of conjugate aggregation. We believe that these measures will help ensure the validity of results. However, to provide further evidence of integrity and comparability of results from each site, we will request that all participating sites enrol in the Wales External Quality Assurance Scheme (WEQAS) Point of Care Quality Assurance Scheme. WEQAS will provide a sample for analysis to each site bimonthly, and provide reports on analyser performance and variability.^8^

#### Data collection

##### Data for prognostic model validation and update of health economic model

We will collect data on all of the candidate predictors considered for inclusion in the prognostic model developed in the IPD meta-analysis (quantitative fFN concentration, previous spontaneous preterm labour, gestation at fFN test, age, ethnicity, body mass index, smoking, deprivation index, number of uterine contractions in set time period, cervical dilatation, vaginal bleeding, previous cervical treatment for cervical intraepithelial neoplasia, cervical length (measured by transvaginal cervical length; when available), singleton/multiple pregnancy, tocolysis and fetal sex). Outcome data will include gestational age at delivery, date and time of delivery, administration of treatments for preterm labour (steroids, antibiotics, tocolysis, magnesium sulfate) duration hospital admission, hospital transfer, onset of labour (preterm prelabour rupture of membranes, idiopathic preterm birth, medically indicated preterm birth (and indication)), place of delivery (base hospital, other hospital, outwith hospital), mode of delivery, neonatal admission, neonatal complications, perinatal mortality, congenital anomaly, sex and birth weight.

Screening data and data about quantitative fFN testing will be collected on paper-based CRFs and research midwives will input these into the web-based electronic database. Clinical outcome data will be collected from the medical records.

#### Maternal acceptability and anxiety

Maternal anxiety will be measured pretest and post-test (24–48 hours) using the validated STAI questionnaire. Acceptability of fFN testing and the decision support will be assessed using follow-up interviews (face to face or telephone, according to maternal preference) which will be conducted with a subgroup of participants (n=30) purposively sampled and stratified according to geographical location, outcome (preterm labour or not) and anxiety scores. Acceptability will also be assessed in a cohort of clinicians (n=30).

#### Statistics and sample size calculation

Guidance for external validation suggests at least 10 events (preterm delivery within 7 days of test) are required for each covariate included in a prognostic model.^9 10^ Data from the cohorts included in our IPD meta-analysis suggest an event rate of between 6% and 12%.^1^ Based on these estimates a sample size of 1600 will provide 96 and 192 events (preterm delivery within 7 days).

A UK study has shown that 8.9% of pregnant women present with symptoms of preterm labour and are eligible for quantitative fFN,^11^ and we anticipate 50% recruitment rate is achievable, thus, overall 4.5% of maternities could be recruited. We will initially include eight units in the cohort study with a combined delivery rate of approximately 36 000 per annum. We anticipate that we will achieve target recruitment within 12 months (1 year x 36 000 x 0.089 x 0.5=1602). If, however, the recruitment rate or event rate is lower than predicted, we will increase the number of sites included in the study and/or the recruitment period, to ensure that a minimum of 60 events (preterm delivery within 7 days of test) are achieved, allowing for external validation of at least six covariates in our model.

It is possible that the IPD meta-analysis will find there is potential added value of combining quantitative fFN testing with cervical length measurement.^12 13^ As cervical length measurement has significant resource requirement (estimated NHS cost £68.16 per test) and lack of out-of-hours provision further limits availability in many NHS hospitals, we think it is very unlikely that cervical length scanning will improve performance of the prognostic model to such a degree as to make it cost-effective. We will assess the incremental costs and effects of cervical length measurement in the proposed health economic model performed in parallel with the IPD meta-analysis, and will feed into design considerations during the first iteration of the prognostic model.

If inclusion of cervical length ultrasound is found to be potentially cost-effective, we will assess the feasibility of including it in the prospective cohort study. We anticipate that including cervical length measurement in the prospective cohort study would be extremely difficult in the current NHS setting as the majority of units do not have 24 hours availability of transvaginal ultrasound and/or trained personnel to perform scans. Inclusion of cervical length would also likely decrease recruitment rate (due to need for additional transvaginal ultrasound examination) and require significant additional resources.

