#### Analysis

##### Validation of prognostic model

The prognostic model developed in the IPD will be externally validated using data collected in the prospective cohort data, using the measures of discrimination and calibration described in QUIDS Protocol part 1,^1^ including R^2^, C statistic, calibration slope, calibration in the large and calibration plots of observed versus predicted risks across deciles (with Loess smoother). The average performance of the model will be summarised across the centres in the cohort study. Between-centre heterogeneity in performance will also be summarised, and reduced (if necessary) by recalibration techniques regarding the strategy for the choice of baseline risk (intercept). That is, the predictor effects will not be modified from the IPD meta-analysis model, but the intercept may need to be tailored to improve validation in UK centres (eg, for rural settings). Based on the findings, a final model and its implementation strategy will then be recommended for use.

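### The 60-event minimum is justified by 10 events per covariate, but the validation re-estimates no covariate effect, so the claim about six covariates does not describe what the design delivers

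*Protocol article*

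**What the plan says.** Protocol article, Statistics and sample size calculation. The one adequacy criterion stated is a rule of thumb: "Guidance for external validation suggests at least 10 events (preterm delivery within 7 days of test) are required for each covariate" in the model. The earlier cohorts "suggest an event rate of between 6% and 12" per cent, so "a sample size of 1600 will provide 96 and 192 events (preterm delivery within 7 days"). Recruitment is projected from 36 000 deliveries a year, ending in "0.089 x 0.5=1602" women in 12 months. If recruitment or the event rate is below prediction, sites or time will be added "to ensure that a minimum of 60 events (preterm delivery within 7 days of test) are achieved", and this number is described as "allowing for external validation of at least six covariates in our model".

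Protocol article, Validation of prognostic model. The measures to be reported are R², the C statistic, calibration slope, calibration in the large and calibration plots. Performance is averaged over centres, and between-centre heterogeneity is summarised. On updating the model, the section states that "the predictor effects will not be modified from the IPD meta-analysis model"; only the intercept may be tailored, with rural settings given as an example.

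**The concern.** The two sections do not fit together. Events per covariate is a criterion for estimating coefficients. Here the coefficients arrive fixed from QUIDS part 1, each woman contributes one predicted risk, and the cohort asks how well those risks rank and match the outcomes. A 6-covariate and a 16-covariate model with the same distribution of predicted risk would be validated with the same precision by the same 60 events.

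The floor is the number of events the study promises to secure if things go badly. It is 37.5% below the lower planning figure of 96. Its stated justification does not tell the reader how precisely the planned performance measures would be known at that point, yet a final model and implementation strategy are to be recommended from those measures.

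**Working it through.** **1. The plan's own figures.** All reproduce.
- 1600 × 0.06 = 96 and 1600 × 0.12 = 192 events.
- 36 000 × 0.089 × 0.5 = 1602 women.
- 60 / 10 = 6 covariates.
- (96 − 60) / 96 = 37.5%.
- Sixty events arise from 60 / 0.06 = 1000 women at 6%, from 60 / 0.12 = 500 at 12%, or from 1600 women at 60 / 1600 = 3.75%.

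**2. Where the covariate count could enter.** Under the article's rule, 96-192 events would correspond to 9.6-19.2 covariates and 60 events to six. The data collection section lists 16 candidate predictors, and the article does not say how many the model will retain. If more than six were retained, 60 events would fail the rule; if six or fewer, it would pass. In neither case would the precision of the validation measures change, because none of the formulas below contains the number of covariates.

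**3. Analytic precision.** Let n be the number of women, φ the event proportion, E = nφ the events and C the C statistic. The documents give φ (6% to 12%). They give no anticipated C, so 0.70, 0.80 and 0.90 are assumed, with a correctly calibrated model and a normally distributed linear predictor (LP).
- C statistic (Newcombe): SE = √{ C(1−C)[1 + (n/2−1)(1−C)/(2−C) + (n/2−1)C/(1+C)] / [n²φ(1−φ)] }. For C = 0.80, n = 1000, φ = 0.06: the bracket is 1 + 499 × 0.2/1.2 + 499 × 0.8/1.8 = 305.9; SE = √(0.16 × 305.9 / 56 400) = 0.0295; half-width 1.96 × 0.0295 = 0.058.
- Observed/expected ratio (O/E), a ratio form of calibration in the large: SE(ln O/E) = √[(1−φ)/E]. For E = 60, φ = 0.06: √(0.94/60) = 0.125, giving exp(±1.96 × 0.125) = 0.78-1.28.
- Calibration slope: SE from the inverse Fisher information of a logistic model with an intercept and LP.

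95% half-widths over assumed C of 0.70-0.90 (at 60 events, over both 6% and 12%):

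| Events | C statistic | Slope | O/E interval |
|---|---|---|---|
| 60 | 0.042-0.070 | 0.21-0.39 | about 0.78-1.28 |
| 96 (n=1600, 6%) | 0.033-0.054 | 0.16-0.29 | 0.82-1.21 |
| 192 (n=1600, 12%) | 0.024-0.039 | 0.13-0.22 | 0.88-1.14 |

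For illustration, a slope half-width of 0.2 would need about 64 to 227 events, depending on C and φ.

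**4. Simulation under the same assumptions.** Central 95% sampling ranges at 60 events:
- slope: about 0.62-1.41 (C = 0.70), 0.76-1.29 (C = 0.80), 0.8-1.27 (C = 0.90);
- O/E: about 0.77-1.25;
- C statistic: about ±0.07 (C = 0.70) to ±0.04 (C = 0.90).

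For C = 0.80 the slope range narrows to about 0.81-1.22 at 96 events and 0.86-1.17 at 192. A re-run with 3000 replicates agreed to within about 0.03 on the slope limits. It gave similar widths whether the 60 events came from 1000 women at 6% or 1600 at 3.75%.

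**5. Per centre.** With eight equal centres the averages are 60/8 = 7.5 events at the floor, and 96/8 = 12 to 192/8 = 24 at the planned size.

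**The case against.** The strongest reply is that the study does not aim at 60 events. It aims at 1600 women and 96-192 events, and 60 is a backstop. At the planned numbers the main validation is reasonably precise: with C = 0.80, the C statistic is known to within about 0.05. This stands, and it confines the point to the floor.

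Two stronger readings are tempting, and the article supports neither.
- A reader might infer that the whole sample size rests on the events-per-covariate rule, since the rule opens the section. But 1600 is linked to no covariate count and matches the recruitment yield of 1602.
- A reader might infer that 60 events is the sole trigger for adding sites or time. The stated trigger is a recruitment or event rate below prediction; 60 is the minimum to be secured once that happens. The Setting section separately allows extra units in order to raise recruitment.

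It can also be said that the article elsewhere speaks of refining or revising the model, which might bring coefficient estimation back in. The validation section limits such change to the intercept.

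On centres, the article promises only to summarise heterogeneity and tailor the intercept if necessary, with no centre-level test or precision, and it plans at least eight sites of unstated size. The figure of 7.5 events per centre is thus illustrative.

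Finally, expected interval widths may sit in a fuller protocol or analysis plan, so their absence here is not the fault. Nor can the guidance cited for the rule be checked. Neither affects the mismatch between the two sections.

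**Conclusion.** Wrong as written, and confined to the floor. Sixty events does not allow external validation of six covariates, because no covariate effect is estimated; what is validated is the set of predictions from one fixed model. Whether 60 is enough depends on the number of events and the spread of predicted risk. At that floor, even a perfectly calibrated model could return a slope anywhere from about 0.62-1.41 (C = 0.70) to about 0.8-1.27 (C = 0.90), and an O/E of about 0.77-1.25.

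The mismatch follows from the article's text alone. The widths rest on assumed values of C, a normal linear predictor and correct calibration, so they show scale and are not predictions. The point changes no endpoint, estimator or analysis, and the planned 96-192 events are not called into question.

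**What to change.** In the sample size section, delete the claim about six covariates. Justify the minimum number of events by the expected precision of the C statistic, calibration slope and O/E (calibration in the large), stating the C statistic and event rate assumed. Choose the floor from the width judged acceptable for those measures.

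If 60 is kept, state the wide intervals it gives, and describe any centre-level intercept tailoring at that floor as exploratory.

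The cost is rewording. The stated adequacy of the floor becomes less favourable. No extra women are needed if 60 is kept and only its justification is restated; a higher floor would bind only if recruitment or the event rate fell short.
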